## 6. Description of population to be studied

Sixty healthy subjects aged 19-50 years will be recruited primarily from employees or students at Haukeland University Hospital or the University of Bergen. Subjects will be briefly informed of the nature of the study in a lecture and by the subject information letter. They will be enrolled during subsequent one to one interviews when they will receive a detailed explanation of the study protocol. If the subject meets the inclusion and does not meet the exclusion criteria and signs the informed consent form, they will be enrolled in the trial and allocated a unique subject identification number. Subjects will be considered eligible to enter the study provided they satisfy the following criteria:

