### Inclusion criteria

- Healthy volunteers (as concluded from the medical history, physical examination, and clinical judgment) who are between 19 and 50 years old
- Females using a reliable method of contraception (from 4 weeks prior to the first vaccination until 4 weeks after the second vaccination) and a negative urine pregnancy test
- Signed informed consent

will be required before administration of each dose of vaccine

- Subjects able to understand and comply with the study protocol and complete the Adverse Event Form

- Subjects able to attend the scheduled visits
- Subjects with normal pre-screening values. If a subjects prescreening samples lie outside the reference values he/she will only be included in the study based upon the medical evaluation of the clinical investigator

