## 5 TRIAL DESIGN

- Investigate the long lasting immunity induced by the vaccine
- Examine the ability of the vaccine to induce cross-reactive immunity to H5 strains of different clades
- Evaluate the quality of the immune response induced by the vaccine.

1. A specific statement of the primary endpoints and secondary endpoints to be measured by the trial

The primary endpoints of the trial are the local and systemic adverse events and tolerability of parenterally administered virosomal H5N1 influenza vaccine with or without 3rd generation ISCOMTM adjuvant. The secondary endpoints are the evaluation of the immunogenicity of a non-adjuvanted and 3rd generation ISCOMTM adjuvanted virosomal H5N1 influenza vaccine and the ability of the vaccine to meet the CHMP evaluation criteria.

The immunogenicity of the H5N1 vaccine will be assessed through the induction of specific local and systemic antibody and cellular immune responses, and analyses of the epitopes to which the response is directed. Furthermore the capacity of the vaccine to elicit cross reactive and long lasting immunity will be evaluated. In a pandemic situation, an important aspect is the rapidity of the immune response to the H5N1 vaccine and therefore the detailed kinetics of the immune response will be investigated.

A description of the type/design of trial to be conducted

The clinical trial will be an open phase I dose escalating pilot study in 60 healthy subjects aged 19-50 years who will receive two doses of vaccine, separated by 21 ± 4 days, by intramuscular injection into the deltoid muscle. Escalating doses will be separated by a period of one week. Four groups of 15 subjects will receive two doses of pandemic virosomal A/H5N1 influenza vaccine containing

|         |                                                                                  |
|---------|----------------------------------------------------------------------------------|
| Group 1 | 30µg HA IM,                                                                      |
| Group 2 | 1.5µg HA adjuvanted with 50µg 3 rd generation ISCOM TM IM, |
| Group 3 | 7.5µg HA adjuvanted with 50µg 3 rd generation ISCOM TM IM, |
| Group 4 | 30µg HA adjuvanted with 50µg 3 rd generation ISCOM TM IM.  |

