## 6 Selection and Withdrawal of subjects

### 1. Subjects inclusion criteria

- The following subjects will be considered eligible to enter the study or receive the second dose of vaccine:
- Healthy volunteers (as concluded from the medical history, physical examination, and clinical judgment) aged 19 to 50 years old
  - Females using a reliable method of contraception (from 4 weeks prior to the first vaccination until 4 weeks after the second vaccination) and a negative urine pregnancy test will be required before administration of each dose of vaccine
  - Signed informed consent
  - Subjects able to understand and comply with the study protocol and complete the Adverse Event Form
  - Subjects able to attend the scheduled visits

- Subjects with normal pre-screening values. If a subjects prescreening samples lie outside the reference values he/she will only be included in the study based upon the medical evaluation of the clinical investigator

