## 7. Treatment of Subjects

1. Treatment to be administered including name of all products, the doses, the dosing schedule, the route of administration and the treatment periods including follow-up periods for the subjects for each product treatment group.

Sixty healthy subjects aged 19-50 years who will receive two doses of H5N1 influenza vaccine by intramuscular injection into the deltoid muscle, separated by  $21 \pm 4$  days. Escalating doses will be separated by a period of one week. Four groups of 15 subjects will receive two doses of pandemic virosomal A/H5N1 influenza vaccine containing

|         |                                                                     |
|---------|---------------------------------------------------------------------|
| Group 1 | 30µg HA IM,                                                         |
| Group 2 | 1.5µg HA adjuvanted with 50µg 3 rd generation ISCOM™ IM, |
| Group 3 | 7.5µg HA adjuvanted with 50µg 3 rd generation ISCOM™ IM, |
| Group 4 | 30µg HA adjuvanted with 50µg 3 rd generation ISCOM™ IM.  |

The second vaccine dose will contain the same quantity of antigen and adjuvant as in the first dose. Each subject will be enrolled in the trial for 1 year. They will be involved in the trial for a period of 10 weeks, during which blood samples will be collected at days 0, 3, 7, 14 and 21 days after each dose of vaccine. All subjects will be asked to voluntarily provide trial blood samples at 6 and 12 months after first dose of vaccine to examine the longevity of the antibody response.

Subjects will be pre-screened to ensure that they meet the entry criteria, and screened during the study for haematological, biochemical and immunological parameters to evaluate any systemic adverse events reactions.

The following parameters will be studied

- **Haematology:** red blood cell count, white blood cell count, % of neutrophils, eosinophils, basophils, monocytes, lymphocytes, platelets, haemoglobin haematocrit, mean cell volume
- **Biochemical parameters:** CRP, transaminases (ASAT, ALAT), alkaline phosphatase, Gamma GT, total bilirubin, total protein, albumin, glucose, blood creatinine, blood urea,
- **Immunology tests:** ANA antibodies

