**2. The number of subjects planned to be enrolled and reason for choice of sample size**

Sixty young healthy subjects (aged 19-50 years old) will be randomly assigned to one of four groups, each group will contain 15 subjects and the investigators will aim to have an equal distribution of males and females in each group and similar age distribution.

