## Appendix

## CASE REPORT FORM

Deltager ID # \_\_\_\_\_

Kjønn \_\_\_\_\_

Alder \_\_\_\_\_

Initialer \_\_\_\_\_

Ansvarlig lege \_\_\_\_\_

Avdeling \_\_\_\_\_

Dato for innrulling i studien \_\_\_\_\_

Relevant sykehistorie (kommentarer) \_\_\_\_\_

Faste medisiner \_\_\_\_\_

Tidligere vaksinert mot influensa (år) \_\_\_\_\_

Antatt influensa siste 12 måneder \_\_\_\_\_

Bekreftet med laboratorieprøve (Ja/nei) \_\_\_\_\_

DERSOM DELTAKEREN TREKKER SEG/ BLIR TRUKKET FRA STUDIEN: \_\_\_\_\_

dato \_\_\_\_\_

årsak ( bare hvis prosjektledeisen har bestemt at deltakeren må forlate studien) \_\_\_\_\_

**INKLUSJONSKRITERIER:** Alle setninger må besvares med JA for at personen skal kunne delta i studien

|                                                                                                                                      |    |     |
|--------------------------------------------------------------------------------------------------------------------------------------|----|-----|
|                                                                                                                                      | Ja | Nei |
| Signert informert samtykke                                                                                                           |    |     |
| Frisk                                                                                                                                |    |     |
| Mellom 20 og 40 år                                                                                                                   |    |     |
| Kvinne: Bruker en pålitelig prevensjonsmetode så lenge studien pågår (fra 4 uker før 1. vaksinasjon til 4 uker etter 2. vaksinasjon) |    |     |
| I stand til å møte på oppsatte tidspunkt, og følge gitte instruksjoner                                                               |    |     |

**EKSKLUSJONSKRITERIER:** Alle setninger må besvares med NEI for at personen skal kunne delta i studien

|                                                                            |     |    |
|----------------------------------------------------------------------------|-----|----|
|                                                                            | Nei | Ja |
| Tidligere anafylaktisk sjokk eller alvorlige komplikasjoner etter vaksiner |     |    |
| Kjent allergi overfor innholdstoffer i vaksine                             |     |    |

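### The case report form's enrolment checklist requires age 20 to 40, while the protocol body admits 19 to 50 throughout; the two must be reconciled before pre-screening

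*Protocol*

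**What the plan says.** The inclusion criteria in section 2 of the Protocol (item 6) admit healthy volunteers "who are between 19 and 50 years old". Section 6, item 1, repeats the criterion as "aged 19 to 50 years old". The same range appears in the population description in section 2, in section 5 (Trial Design), in section 7 (Treatment of Subjects) and in the sample size paragraph of section 10.

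The Appendix contains the case report form in Norwegian. The inclusion list on its enrolment page carries the instruction "Alle setninger må besvares med JA for at personen skal kunne delta i studien" (every statement must be answered yes for the person to be able to take part). The third statement on that list is "Mellom 20 og 40 år". The form's checklists for the first and second vaccination days have no age line.

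**The concern.** An inclusion checklist is where eligibility is put on record for each subject, so it should carry the same criteria as the protocol. Here it does not, and for anyone aged 19 or 41 to 50 neither course is clean.

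- **Form followed.** A volunteer who meets the protocol's age criterion is refused. The 41 to 50 band then drops out of the safety and immunogenicity data without any protocol decision to remove it.
- **Protocol followed.** The volunteer is enrolled, but the enrolment page shows a no against an item that it treats as a condition of taking part.
- **Both followed, by different staff.** Selection by age becomes inconsistent. Age matters to the design to the extent that sections 5 and 10 aim for vaccine groups of similar age.

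The form has standing. Section 11 counts case report forms among the paper records treated as source documentation, and section 14 makes the clinical investigators answerable for their accuracy. The age item is on the enrolment page only, so no later checklist would bring the conflict to light.

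**Working it through.** The protocol has no figure of its own to reproduce on this point. The check is a comparison of text followed by a count of whole years of age.

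**Statements of the age range**

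| Place in the Protocol | Text |
|---|---|
| Section 2, item 6, population | "Sixty healthy subjects aged 19-50 years will be recruited primarily from employees or students" |
| Section 2, inclusion criteria | "who are between 19 and 50 years old" |
| Section 5, design | "60 healthy subjects aged 19-50 years who will receive two doses of vaccine" |
| Section 6, item 1, inclusion criteria | "aged 19 to 50 years old" |
| Section 7, treatment | "Sixty healthy subjects aged 19-50 years who will receive two doses of H5N1 influenza vaccine" |
| Section 10, sample size | "Sixty young healthy subjects (aged 19-50 years old) will be randomly assigned to one of four groups" |
| Appendix, case report form, enrolment checklist | "Mellom 20 og 40 år" |

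Six statements agree and one differs. The differing row is intact and sits between other intact rows, so it is not a fault of text extraction, and it is current text, not an amendment log.

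**Count of ages, end points included**

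- Protocol range: 50 − 19 + 1 = 32 whole years.
- Form range: 40 − 20 + 1 = 21 whole years.
- Admitted by the protocol but failing the form: 32 − 21 = 11 years, namely age 19 (1 year) and ages 41 to 50 (10 years).
- Share: 11 / 32 = 34.4%.

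**If the form's wording is read as excluding its end points**

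- Form range 21 to 39: 39 − 21 + 1 = 19 whole years.
- Failing the form: 32 − 19 = 13 years, and 13 / 32 = 40.6%.

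**Direction of the mismatch.** On either reading the form's range lies wholly inside the protocol's. Following the form therefore enrols nobody of an age that the protocol excludes.

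**Number of subjects.** The share of years is not a share of people. The protocol gives no age distribution and says only that recruitment is mainly from employees and students of the hospital and the university. If the form is followed, none of the 60 enrolled is outside 20 to 40, and the effect falls on an unknown number of people refused. If the protocol is followed, the number enrolled with a no on the form could lie anywhere from 0 to 60.

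**The case against.** The strongest case against giving this weight is that the governing criterion is clear. The body states it six times without variation, and the exception is one line in an appended form. The narrower range adds no risk to subjects. No objective or analysis is described for the 41 to 50 band, and similar age across groups can be achieved under either range. Section 10 describes a small phase I study to be followed by a larger one, so some loss of generalisability is tolerable. The adverse event form in the same Appendix is pre-printed with the year 2006 although the protocol cites 2008 sources, which fits templates carried over from earlier work, though the document does not say so.

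Most of that stands, and it limits the weight of the point. It does not remove the contradiction, because the line is a stated condition of participation and nothing tells staff which range prevails.

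Three stronger readings are tempting, and the document does not support them.

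- A reader might infer that every subject aged 19 or 41 to 50 would become an eligibility violation. Section 8 ties deviations to the approved protocol, and a 45-year-old meets its age criterion. What results is a mismatch between form and protocol that needs a query or a note.
- A reader might assume that site staff decide eligibility from the form. The form's instruction makes this plausible. However, section 2 and the description of the first visit in section 5 make enrolment depend on the inclusion and exclusion criteria, and the latter has the visit's procedures then recorded in the form.
- A reader might scale 34% of the years to about 21 of 60 subjects (60 × 11 / 32 = 20.6). That requires ages spread evenly from 19 to 50, for which the protocol gives no basis.

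**Conclusion.** The point holds as an internal inconsistency of moderate severity. A mandatory item on the enrolment checklist contradicts the age criterion stated six times in the protocol body, and 11 of the 32 admitted years of age (34%) fall in the gap. The figure assumes whole years with end points included; it rises to 13 of 32 (41%) if the form's limits are read as exclusive. No number of affected subjects can be given.

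This is not a criticism of the design, which is consistent in the body. Sample size, power and error rates do not change. At stake are the age coverage of the results and an eligibility record that agrees with the protocol.

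**What to change.** Before pre-screening starts, change the age line on the enrolment checklist of the case report form to *Mellom 19 og 50 år*, so that it matches sections 2, 5, 6, 7 and 10. If 20 to 40 was the intended population, amend all six statements in the body instead and leave the form as it is. Either way, the sponsor should confirm which range was intended.

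Correcting the form costs one line. Done later it cannot fully repair the record, since a volunteer already refused is lost and an enrolment page already marked no needs an explanation.

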# Resultat av blodprøver

Deltagers ID # \_\_\_\_\_ Kjønn \_\_\_\_\_ Alder \_\_\_\_\_ Initialer \_\_\_\_\_

|  |    |           |           |                 |  |  |                      |                     |                      |  |       |                      |                     |                      |  |        |                      |                     |                      |  |        |                      |                     |                      |  |        |                      |                     |                      |  |  |  |
|--|----|-----------|-----------|-----------------|--|--|----------------------|---------------------|----------------------|--|-------|----------------------|---------------------|----------------------|--|--------|----------------------|---------------------|----------------------|--|--------|----------------------|---------------------|----------------------|--|--------|----------------------|---------------------|----------------------|--|--|--|
|  | OK | resultat? | kommentar | Dag -14-
-12 |  |  | Hematologiske prøver | Bio kjemiske prøver | Immunologiske prøver |  | Dag 3 | Hematologiske prøver | Bio kjemiske prøver | Immunologiske prøver |  | Dag 21 | Hematologiske prøver | Bio kjemiske prøver | Immunologiske prøver |  | Dag 24 | Hematologiske prøver | Bio kjemiske prøver | Immunologiske prøver |  | Dag 42 | Hematologiske prøver | Bio kjemiske prøver | Immunologiske prøver |  |  |  |
|  |    |           |           |                 |  |  |                      |                     |                      |  |       |                      |                     |                      |  |        |                      |                     |                      |  |        |                      |                     |                      |  |        |                      |                     |                      |  |  |  |
|  |    |           |           |                 |  |  |                      |                     |                      |  |       |                      |                     |                      |  |        |                      |                     |                      |  |        |                      |                     |                      |  |        |                      |                     |                      |  |  |  |

## Bivirkninger vurdert av lege: medikament

| DATO | ANTALL
DAGER
ETTER
VAKSINASJ
ON
(1./2. dose) | BIVIRKNING | SAMMENHENG
MED
VAKSINASJON
1: relatert
2: ikke relatert | EVENTUELLE
MEDIKAMENT
TATT I
FORBINDELSE
MED
BIVIRKNINGEN | VIDERE OPPFØLGING | KOMMENTARER
(Angi alvorlighetsgrad, og om hendelsen er meldt videre) | SIGN
LEGE
DATO |
|------|-------------------------------------------------------------|------------|---------------------------------------------------------------------|--------------------------------------------------------------------------|-------------------|-------------------------------------------------------------------------|----------------------|
|      |                                                             |            |                                                                     |                                                                          |                   |                                                                         |                      |
|      |                                                             |            |                                                                     |                                                                          |                   |                                                                         |                      |
|      |                                                             |            |                                                                     |                                                                          |                   |                                                                         |                      |
|      |                                                             |            |                                                                     |                                                                          |                   |                                                                         |                      |
|      |                                                             |            |                                                                     |                                                                          |                   |                                                                         |                      |

**Norwegian Adverse Event Form**

Deltager ID #: \_\_\_\_\_

STARTDATO (Dag 0): \_\_\_\_ / \_\_\_\_ /2006

Vaksinedose: \_\_\_\_\_

## SKJEMA FOR EGENRAPPORTERING AV BIVIRKNINGER/REAKSJONER ETTER INFLUENSAVAKSINASJON MED H5N1 VAKSINE

MERK AV I DE RUBRIKKENE SOM PASSER. Grader fra 1-3

1= Svake/ ubetydelige symptomer som ikke gir særlige plager.

2= Symptomer som er så besværlige at de påvirker den daglige aktiviteten, men som ikke krever legetilsyn.

3= Sterke eller vedvarende symptomer som i høy grad påvirker den daglige aktiviteten, eller som krever legetilsyn.

Tom rubrikk betyr "intet å melde". DET ER PÅ BAKSIDEN AV SKJEMAET. Reaksjoner som ikke er nevnt i tabellen: Bruk kommentarfeltet. Angi også i samme kommentarfelt om du har tatt noen medisiner som en følge av reaksjonene, og i så fall hvilke medisiner.

Ved akutt legebehov, se telefonliste på baksiden av skjemaet. Ved bruk av annen lege: Meld fra om at du er med i denne studien.

Skjemaet bringes med til klinikken og vises legen ved hvert fram møte (dagene skravert på skjemaet).

| Dag etter vaksinasjon | Lokale symptomer på injeksjonsted |         |        |                     |          | Generelle symptomer     |                       |           |          |          |        |            |              | Andre hendelser |                                    |       |
|-----------------------|-----------------------------------|---------|--------|---------------------|----------|-------------------------|-----------------------|-----------|----------|----------|--------|------------|--------------|-----------------|------------------------------------|-------|
|                       | Rødhet                            | Hevelse | Smerte | Liten blodutredelse | Hard hud | Feber >38°C (angi temp) | Uvel (beskriv under ) | Skjelving | Tretthet | Hodepine | Svette | Muskelverk | Ledd-smerter |                 | Luftveis-symptomer (beskriv under) | Diaré |
| 0                     |                                   |         |        |                     |          |                         |                       |           |          |          |        |            |              |                 |                                    |       |
| 1                     |                                   |         |        |                     |          |                         |                       |           |          |          |        |            |              |                 |                                    |       |
| 2                     |                                   |         |        |                     |          |                         |                       |           |          |          |        |            |              |                 |                                    |       |
| 3                     |                                   |         |        |                     |          |                         |                       |           |          |          |        |            |              |                 |                                    |       |
| 4                     |                                   |         |        |                     |          |                         |                       |           |          |          |        |            |              |                 |                                    |       |
| 5                     |                                   |         |        |                     |          |                         |                       |           |          |          |        |            |              |                 |                                    |       |
| 6                     |                                   |         |        |                     |          |                         |                       |           |          |          |        |            |              |                 |                                    |       |
| 7                     |                                   |         |        |                     |          |                         |                       |           |          |          |        |            |              |                 |                                    |       |
| 8                     |                                   |         |        |                     |          |                         |                       |           |          |          |        |            |              |                 |                                    |       |
| 9                     |                                   |         |        |                     |          |                         |                       |           |          |          |        |            |              |                 |                                    |       |
| 10                    |                                   |         |        |                     |          |                         |                       |           |          |          |        |            |              |                 |                                    |       |
| 11                    |                                   |         |        |                     |          |                         |                       |           |          |          |        |            |              |                 |                                    |       |
| 12                    |                                   |         |        |                     |          |                         |                       |           |          |          |        |            |              |                 |                                    |       |
| 13                    |                                   |         |        |                     |          |                         |                       |           |          |          |        |            |              |                 |                                    |       |
| 14                    |                                   |         |        |                     |          |                         |                       |           |          |          |        |            |              |                 |                                    |       |
| 15                    |                                   |         |        |                     |          |                         |                       |           |          |          |        |            |              |                 |                                    |       |
| 16                    |                                   |         |        |                     |          |                         |                       |           |          |          |        |            |              |                 |                                    |       |
| 17                    |                                   |         |        |                     |          |                         |                       |           |          |          |        |            |              |                 |                                    |       |
| 18                    |                                   |         |        |                     |          |                         |                       |           |          |          |        |            |              |                 |                                    |       |
| 19                    |                                   |         |        |                     |          |                         |                       |           |          |          |        |            |              |                 |                                    |       |
| 20                    |                                   |         |        |                     |          |                         |                       |           |          |          |        |            |              |                 |                                    |       |
| 21                    |                                   |         |        |                     |          |                         |                       |           |          |          |        |            |              |                 |                                    |       |

Telefon for medisinsk assistanse utenfor kontortid: [name] [name] (mobil [name]) eller sentralbord Haukeland Universitetssjukehus [name], før eller vakthavende lege på infeksjonsmed. avd.

Eventuelle kommentarer:

[illegible]
